### Statistics

Numerical variables will be described with means and SDs, and categorical variables by percentages. The numerical outcomes in this study will be analyzed by a mixed-effect ANOVA model, using treatment and visit as fixed factors, subject as a random factor, and baseline values as covariates. A planned contrast will be used to compare data at month 3 between the groups. Non-normally distributed variables will be log-transformed. Imbalances in the characteristics of the groups at baseline will be included in the ANOVA model as part of a sensitivity analysis. The statistical analysis will be conducted in R 4.1.1 (The R Foundation, Vienna, Austria).

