## Materials and Methods

### Study Design

Patients with PD will be assigned randomly to one of three different training programs (AR-TT, or RNG- TT, or TT alone), which will be performed in a parallel-group design for 3 weeks of 30 min daily for 5 days a week in addition to the regular rehabilitation program (Figures 1, 2). Frequency of falls or near falls (within 3 months before V1) will be used (x > 1 or x = 1) for stratified randomization.

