**Figure 2 F2:**
[figure not shown]
Experimental protocol design. MMSE, Mini-Mental Status Examination; Mini-BEST, Mini-Balance Evaluation Systems Test; SBG, sensor-based gait analyses; FoG, freezing of gait; WOQ-9, Wearing-Off Questionnaire-9; PDQ8, QoL in PD questionnaire; HADS, Hospital Anxiety and Depression Questionnaire; MDS-UPDRS, MDS-sponsored revision of the Unified Parkinson's Disease Rating Scale; CGIC, Clinical Global Impression of Change; TAP, Test Battery of Attentional Performance.

Assessments will be performed by a blinded investigator before the beginning of the training (V1), after 3 weeks of training (V2), and 3 months after training (V3) during the on-phase. The primary outcome will be the frequency of falls or near-falls during 3 months following training compared to the frequency of falls or near-falls in the 3 months before inclusion (AR-TT vs. TT, and RNG-TT vs. TT). Both interventions will be compared in exploratory analyses (AR-TT and RNG-TT).

Secondary outcomes will be the clinical parameters Movement Disorder Society-sponsored revision of the Unified Parkinson's Disease Rating Scale (MDS-UPDRS III-IV) (25), Hospital Anxiety and Depression Questionnaire (HADS) (26), FoG Questionnaire (27), the Mini-Balance Evaluation Systems Test (Mini-BEST) (28), quality of life in PD questionnaire (PDQ-8) (29), Wearing-Off Questionnaire-9 (WOQ-9) (30), and executive function testing by using tests of the Test Battery of Attentional Performance (TAP) (31) assessed at V1, and compared to V2 and V3 (MDS-UPDRS III-IV, HADS, FoG Questionnaire, Mini-BEST only). Clinical Global Impression of Change (CGIC) will be assessed and V2 and V3 (32).

Sensor-based gait (SBG) assessment will be measured and compared before V1, after V2, and before V3 to have more detailed information on gait changes in the natural environment at home. Given the set of parameters described in Section “Gait and Physical Activity Assessment Using Wearable Sensors,” analyses will be conducted to evaluate the sensitivity to change related to a progression in daily-life motor performance following the rehabilitation program. In addition, gait analysis on behalf of the C-Mill data will be collected before and after the intervention during 3 min of comfortable walking (V1 and V2).

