### Patients

In total, 45 PD patients (age 40 or older) with Hoehn and Yahr stages II-IV (only mobile patients with advanced PD), with at least one fall or near-fall within the 3 months before baseline assessment, will be asked for participation when appointed to in-ward neurorehabilitation at the Center for Neurorehabilitation in Valens, Switzerland (Figure 1). Patients shall be able to participate in the treadmill training at high intensity for 3 weeks. Patients with dementia, defined by a Mini-Mental Status Examination (MMSE) test result of <24, will be excluded from participation. The protocol was approved by Ethikkommission Ostschweiz (BASEC ID 2019-01894) and registered at ClinicalTrials.gov (Identifier: NCT04108741).

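### The primary outcome is a fall count that can be zero, but the stated log-transformation rule is undefined for event-free patients, so the estimate depends on an unstated handling of zeros

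*Protocol article*

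**What the plan says.** The Study Design section (text after Figure 2) defines the outcome: "The primary outcome will be the frequency of falls or near-falls during 3 months following training". It is set against the same count over an equally long period ahead of inclusion. The comparisons are "AR-TT vs. TT, and RNG-TT vs. TT".

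The Patients section admits people "with at least one fall or near-fall within the 3 months before baseline assessment", and Study Design says that this frequency "will be used (x > 1 or x = 1) for stratified randomization". A baseline count of exactly one is therefore planned for. Baseline cannot be zero; follow-up can.

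The Statistics section gives one model: "The numerical outcomes in this study will be analyzed by a mixed-effect ANOVA model". Treatment and visit enter it as fixed effects, patients as a random effect, and the baseline measurement as a covariate, with a planned contrast at month 3. Its one remedy for non-normality is "Non-normally distributed variables will be log-transformed". It states no constant, no rule for zeros and no separate model for the falls count.

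The Sample Size section expects reductions of 50% and 25%, but calculates with a difference of 1.5 falls and an SD of 1.16.

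**The concern.** Falls plus near-falls over 3 months is a non-negative and usually right-skewed count, so the log rule would apply to it. For a patient with no event after training the transformed value is minus infinity. In R, the named software, standard model fitting stops with an error on such a response. The analyst must then choose, possibly after seeing the data, between excluding these patients, adding a constant, or leaving the count untransformed.

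The choice is not neutral. Event-free patients are the best responders and are expected more often in the arm that works better. Excluding them removes success differentially. An added constant makes the log-scale contrast depend on its size. At stake is a primary estimate that is not determined by the plan.

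**Working it through.** **1. The plan's own figure.** Inputs from Sample Size: difference 1.5, SD 1.16, two-sided alpha 0.025, power 80%, dropout 10%. The exact two-sample t-test gives power 0.771 at 12 per arm and 0.811 at 13. Then 13/(1 − 0.10) = 14.4, rounded up to 15. The stated 15 per arm reproduces, so the design treats the count as normal on a mean-difference scale.

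**2. Inferred means (assumption).** If 1.5 falls is the gap between the two reductions, the baseline mean is 1.5/(0.50 − 0.25) = 6. The follow-up means are 3.0 (experimental) and 4.5 (control), and their ratio is 3.0/4.5 = 0.667. The document gives no dispersion, so a range from Poisson to negative binomial (NB) size k = 0.5 is shown, with variance μ + μ²/k.

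**3. Chance of no event.** Poisson: P(0) = exp(−μ). NB: P(0) = (k/(k+μ))^k.

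For one baseline event, taken as the patient's rate, Poisson gives exp(−0.5) = 0.61 with a 50% reduction and exp(−0.75) = 0.47 with a 25% reduction.

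At means 3.0 and 4.5, with 30 experimental and 15 control patients:

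| Dispersion | P(0), experimental | P(0), control | Expected event-free of 45 |
|---|---|---|---|
| Poisson | 5% | 1% | 1.7 |
| k = 2 | 16% | 10% | 30 × 0.160 + 15 × 0.095 = 6.2 |
| k = 1 | 25% | 18% | 10.2 |
| k = 0.5 | 38% | 32% | 16.1 |

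The probability of at least one event-free patient is 0.82 under Poisson and above 0.99 in the other rows.

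**4. What each handling of zeros estimates.** Entries are exp(difference in mean log), from 2 million simulated patients per arm; the true ratio is 0.667.

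| Handling | Poisson | k = 2 | k = 1 | k = 0.5 |
|---|---|---|---|---|
| Drop zeros | 0.68 | 0.74 | 0.76 | 0.79 |
| log(y+1) | 0.71 | 0.74 | 0.76 | 0.80 |
| log(y+0.5) | 0.67 | 0.70 | 0.72 | 0.76 |
| log(y+0.1) | 0.61 | 0.62 | 0.64 | 0.69 |
| log(y+0.01) | 0.55 | 0.53 | 0.55 | 0.60 |

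At k = 2, dropping zeros loses 1 − ln(0.74)/ln(0.667), about a quarter of the log effect. The untransformed mean difference comes out at about −1.5, its true value.

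**5. Test behaviour at 13 evaluable per arm** (no baseline adjustment, nominal 0.025). Type I error lies between 0.015 and 0.027 for the raw, log-plus-constant and drop-zeros tests. Power under Poisson is 0.35 (raw), 0.34 (log(y+1)), 0.30 (drop zeros) and 0.35 (quasi-Poisson). At k = 2 it is 0.11, 0.12, 0.09 and 0.12.

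**6. Power on the ratio scale.** n per arm = (z₀.₉₈₇₅ + z₀.₈₀)² × (1/3.0 + 1/4.5 + 2/k)/ln(0.667)², dropping the 2/k term under Poisson. This gives 33 (Poisson), 90 (k = 2), 148 (k = 1) and 264 (k = 0.5) evaluable patients, or 37, 100, 165 and 294 with 10% dropout. Approximate power at 13 per arm is 0.39, 0.14, 0.09 and 0.06.

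**The case against.** A reader might infer that the plan biases the effect toward the null. The document does not fix that. Attenuation follows if zeros are dropped or 1 is added; a constant of 0.1 mostly reverses it, 0.01 fully reverses it, and the untransformed difference is unbiased.

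A reader might also conclude that about half the effect is lost. That needs an assumed mix of half the patients at one baseline event and half at six (k = 2), where dropping zeros gives 0.82 and the variants span 0.54 to 0.82. Its baseline mean is 3.5, so the planned reductions differ by 0.25 × 3.5 = 0.875 falls, not the 1.5 in Sample Size. The one-event stratum shows that such patients are eligible, not that they are half the sample.

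Nor is the ANOVA on a different scale from the sample size: an untransformed contrast matches the 1.5-fall calculation. The low power in the simulations comes mainly from the planning SD of 1.16, which lies below the Poisson minimum for these means (√3.0 = 1.73 and √4.5 = 2.12). The claim that a change score could not be logged is weak, because baseline as covariate points to the follow-up count as the response.

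These limits stand. What does not stand is that the gap is mere detail for an analysis plan. The article states the transformation rule, and the rule fails on its own primary outcome.

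**Conclusion.** The point holds in a limited form. The log rule cannot be applied to event-free patients, at least one of whom is likely in every scenario examined. The estimate then turns on an unstated decision: at an inferred baseline mean of 6 and k = 2, the same true ratio of 0.667 is reported as anything from 0.53 to 0.74. The direction is open and type I error is not materially affected, so this is a defect in what is estimated, not a threat of false positives. Under Poisson with all patients at baseline 6, dropping zeros hardly matters (0.68).

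The sizes rest on the inferred baseline mean and on assumed dispersions; neither is given in the document. That log(0) is undefined rests on no assumption.

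**What to change.** For the primary outcome only, replace the ANOVA and log rule with a prespecified count model:

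- Negative binomial or quasi-Poisson, log link, with the 3-month follow-up count as response.
- Arm, log baseline count and randomisation stratum as covariates, and log follow-up time as offset. The log baseline is defined because entry requires at least one event, provided that the baseline count uses the eligibility window.
- Rate ratios with confidence intervals for AR-TT vs TT and RNG-TT vs TT.
- P-values from a stratified re-randomisation test. Wald tests can be anti-conservative at 13 to 15 per arm: an unadjusted negative binomial Wald test rejected 3.7% of true nulls at nominal 2.5% (1,500 simulated trials, 13 per arm, mean 4.5, k = 2). The exact excess varies with run and fitting method.

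Keep the mixed-effect ANOVA for the repeatedly measured continuous scales. Fix all this before outcome data are seen by arm.

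The analysis itself costs some wording and a few lines of R, with no new data. The real cost is that the effect measure becomes a rate ratio and no longer the 1.5-fall mean difference, so the stated power must be restated on that scale with an explicit dispersion. The change does not itself raise power. The ratio-scale figures above omit baseline adjustment, which would improve them somewhat.

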### Sample Size

According to previous studies, a reduction of 50% in the frequency of falls or near falls can be expected in the two experimental intervention groups vs. a reduction of 25% in the control group. Under the assumption of a difference of 1.5 falls between the respective group and placebo and an SD of 1.16, a sample size of 15 patients in each group is required (alpha = 0.025 two-tailed, power = 80%), i.e., 10% dropouts (G-power) (11).

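### Sensitivity covariates are picked by chance baseline imbalance rather than prognostic value, and the randomisation stratum is not a model term: a minor point, touching the robustness check and the secondary outcomes

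*Protocol article*

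**What the plan says.** The Statistics section of the protocol article gives one model for all numerical outcomes, a mixed-effect ANOVA "using treatment and visit as fixed factors, subject as a random factor, and baseline values as covariates", with a planned contrast between groups at month 3. It then adds that "Imbalances in the characteristics of the groups at baseline will be included in the ANOVA model as part of a sensitivity analysis". It gives no list of characteristics and no criterion for calling a difference an imbalance.

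The Study Design section sets the stratification: "Frequency of falls or near falls (within 3 months before V1) will be used (x > 1 or x = 1) for stratified randomization". The two strata cover everyone, because the Patients section admits only patients "with at least one fall or near-fall within the 3 months before baseline assessment". The stratum is not among the model terms in the Statistics section.

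The primary outcome is falls or near-falls in the three months after training, "compared to the frequency of falls or near-falls in the 3 months before inclusion" (Study Design, outcome paragraph below the Figure 2 legend). The baseline value for the primary outcome is therefore in effect the count from which the stratum is cut. For Mini-BEST, the FoG questionnaire, HADS, MDS-UPDRS and the gait measures, the natural reading of baseline values is each outcome's own baseline, which does not carry fall history.

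**The concern.** There are two separate issues.

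The first is the rule for the sensitivity analysis. With proper randomisation, any baseline difference between arms is a chance event. A variable that differs but does not predict the outcome adds nothing except lost degrees of freedom, which matters with 15 patients per arm. A strong predictor that happens to be balanced is left out, although adjusting for it would help. The content of the robustness check is then unknown until the data are seen, and it cannot serve as a fixed comparator for the main result.

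The second is the stratum. Stratified allocation removes between-arm variation due to the stratum. If the model ignores a stratum that predicts the outcome, that variation stays in the residual and the reported standard errors are too large. At stake are somewhat conservative tests and intervals for outcomes whose covariates do not already carry fall history.

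**Working it through.** **The plan's own figure.** The Sample Size section gives "Under the assumption of a difference of 1.5 falls between the respective group and placebo and an SD of 1.16", so d = 1.5/1.16 = 1.29. With a two-sample t-test at two-sided alpha 0.025 (noncentral t, 2n − 2 degrees of freedom, noncentrality d·√(n/2)), power is 0.771 at n = 12 and 0.811 at n = 13. With 10% dropout, 13/0.9 = 14.4, rounded up to 15. The stated 15 per group is reproduced, and nothing below changes it.

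**Stratum, primary outcome.** Simulation with 15 per arm in three arms, stratified allocation, 4,000 trials and no treatment effect. The overdispersed fall counts are assumed, and put about 81% of patients in the stratum with more than one event. The outcome is the log of (follow-up count + 1), the baseline covariate is the log baseline count, and the nominal level is 0.025.

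| Model covariates | Model SE | Empirical SE | Type I error |
|---|---|---|---|
| Baseline falls (as stated) | 0.2096 | 0.2124 | 0.0253 |
| Baseline falls + stratum | 0.2090 | 0.2124 | 0.0248 |

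The ratio is 0.2096/0.2090 = 1.003, a gain of about 0.3% from adding the stratum.

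**Stratum, secondary outcomes.** Same allocation, 3,000 trials per row. The outcome stands for what remains after its own baseline is removed. The stratum effect is in units of the within-stratum SD and is assumed.

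| Residual stratum effect | Model SE, stratum omitted | Model SE, stratum included | Ratio |
|---|---|---|---|
| 0 | 0.3628 | 0.3631 | 0.999 |
| 0.25 | 0.3653 | 0.3638 | 1.004 |
| 0.5 | 0.3715 | 0.3649 | 1.018 |
| 0.8 | 0.3821 | 0.3638 | 1.050 |

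In the last row the actual scatter of the estimates is nearly the same with and without the stratum (empirical SE 0.3664 and 0.3637), and the type I error without it is 0.018. The error is therefore an overstated standard error, in the conservative direction. It does not make the estimator materially noisier.

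A rough check is √(1 + p(1 − p)g²), with p the share in the higher stratum and g the stratum effect. For p = 0.81 and g = 0.8 it is √(1 + 0.154 × 0.64) = 1.048, in line with the simulation. The split matters: an even split with g = 0.8 gives √(1 + 0.25 × 0.64) = 1.077. The documents do not give the split.

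**Imbalance rule.** As an illustration only, if k independent characteristics were each tested at 5%, the chance of at least one apparent imbalance under perfect randomisation is 1 − 0.95^k. This is 0.40 for k = 10 and 0.54 for k = 15.

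To see what such a rule does to the test, a null simulation used two arms of 15 and 10 assumed candidate covariates, which jointly explained 30% or 50% of the outcome variance. Covariates entered if the arms differed at p < 0.05 or p < 0.10 (6,000 trials per setting, nominal level 0.025):

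- imbalance-adjusted test: type I error 0.015 to 0.021;
- the better of the unadjusted and adjusted results: 0.025 to 0.034.

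The Monte Carlo standard error is √(0.025 × 0.975/6000) = 0.002.

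**The case against.** The imbalance adjustment is expressly confined to a sensitivity analysis, beside a main model and a contrast that are fixed. A reader might infer that the primary result can be steered or its error rate inflated. The document does not support this: nothing in it lets the sensitivity result replace the main one. In the simulation the adjusted test is conservative, and the rise to at most 0.034 needs selective reporting that the document does not propose. This part of the objection stands.

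A reader might also infer that leaving out the stratum costs precision for the primary outcome. It does not, because the baseline count carries the same information.

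For the secondary outcomes, one might suppose that the stratum explains 10 to 20% of residual variance, so that including it would shorten intervals by 5 to 11% (√0.90 = 0.95, √0.80 = 0.89). That would need a difference between strata, after adjustment for the outcome's own baseline, of about 0.85 to 1.27 SD with the 81/19 split, or 0.67 to 1.0 SD with an even split. The documents give no reason to expect effects of that size.

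The 40 to 54% chance of an imbalance likewise presumes independent variables and a 5% test. The plan states neither, and Parkinson's disease measures such as stage, balance and freezing are likely to be correlated.

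Finally, covariate lists and stratum terms are often left to a full protocol or analysis plan, which is not shown. That excuses the missing list and threshold. It does not excuse the selection principle, which the article states: a plan that added a threshold would still choose covariates because the arms differ. The model terms are stated too, without the stratum.

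**Conclusion.** The point holds in a limited form. The stated rule makes the robustness check depend on chance differences in the data, and the stated model does not include the stratification factor. The primary type I error is not affected, and the primary standard error changes by about 0.3%. For secondary outcomes adjusted only for their own baseline, standard errors may be about 0 to 5% too large, on the safe side.

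That range rests on assumed residual stratum effects of 0 to 0.8 SD and an assumed 81% of patients with more than one event. A more even split would raise its upper end somewhat. The primary-outcome figure rests on an assumed count distribution and on reading the baseline values for the primary outcome as the pre-inclusion fall count, which is what the text suggests. The point is worth correcting because the correction is nearly free, not because the harm is large.

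**What to change.** 1. Add the stratum (one versus more than one fall or near-fall) as a fixed factor. It matters mainly for the secondary outcomes; in the primary model it is harmless and keeps the analysis aligned with the randomisation. Cost: one degree of freedom. With no stratum effect, the simulated standard error rose by about 0.1%.
2. Replace the imbalance rule by a short list of prognostic covariates already collected, for example Hoehn and Yahr stage, baseline FoG score and baseline Mini-BEST. Fix the list before unblinding and use it in the sensitivity analysis whatever the balance turns out to be. Keep it short, since each term costs a degree of freedom with 15 patients per arm.
3. State that the main model remains the basis for the conclusion whatever the sensitivity analysis shows.

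This is a change of wording in the analysis plan. It needs no new data and no change to the sample size.

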## Results

In a randomized-controlled study with a parallel-group design, one of the three interventions will be applied over 3 weeks during regular neurorehabilitation with a follow-up of three months (AR-TT vs. RNG-TT vs. TT). Cognitive executive performance, anxiety, FoG, motor function, gait analyses, and functional gait testing will be controlled. In addition, wearable sensors will allow for the quantification of gait performance during daily living.

We expect the participation of 45 patients with a similar distribution of falls and further baseline factors in the three intervention arms. We assume that dual-task training with both executive and perceptual concurrent tasks leads to better gait performance than TT alone. Secondary outcome measures were chosen to elucidate influencing factors (executive function, mood, and motor function) and to show training effects on further outcomes (i.e., gait speed and clinical gait testing). We hope that SBG analyses will reveal which intervention has more impact on improving gait stability, on FoG, and on gait performance in daily life.

## Discussion

This study examines the effects of dual-task training added to HIT TT on falls and gait in PD. It assesses whether motor-perceptual dual-task training by means of AR (AR-TT) and a highly demanding motor-executive DT, i.e., the generation of a random number at every right foot placement (RNG-TT), can realize further improvements over TT alone.

Already TT, especially at high intensity, has a marked influence on the reduction of falls (17, 33). The additional interventions use different strategies (perceptual or executive) to increase neuroplasticity. Both shall further increase the ability to react toward sudden obstacles by training either perceptual or executive DT. The previous AR-TT study revealed reduced falls as compared to TT during a follow-up of 6 months (17) presumably due to a reduced cognitive frontal load (i.e., more capacity for executive reactions) and due to an increased cerebellar motor control (11). This study aims at enhancing the effects of AR-TT on gait in a shorter but more intense training period by using programs adapted for PD patients with a balance disorder. In addition, in a third arm, RNG will be probed as an executive-cognitive task to further improve baseline TT.

Which of the additional training paradigms will have more advantages compared to TT alone will be elucidated in the present study. Previous investigations revealed that cognitive training in PD should have a game-like character comparable to commercially available games [Nintendo –wii; (50)]. We assume that the game-like character of RNG may exhibit a powerful effect on the ability of a patient for DT. In fact, RNG studies demonstrated that performance decrements on the simultaneous motor task are considerable, even in healthy subjects. Diverse kinds of motor tasks were investigated, from simple finger tapping (51), key pressing (52), and mouse clicking (24) to grooved pegboard performance (53), pursuit tracking (54) and bimanual coordination (55). Apart from the study cited in the introduction section (21), walking was not specifically investigated, but other complex motor coordination tasks, such as car driving (56), to which RNG introduced more jerky actions. For the influence of RNG on the performance of patients with PD on other cognitive tasks see Witt et al. (57) and Robertson et al. (58). To the (pronounced) degree that RNG interferes with motor execution, we would expect the training of DT based on RNG during locomotion also to lead to a pronounced improvement in everyday gait performance. On the other hand, AR-TT has various advantages compared to executive DT. The game-like character and the diversity of different motor tasks are important features to enhance cognitive and motor neuroplasticity in patients with PD suffering from reduced and slowed motor reactions.

The study further assesses the conditions and influencing factors underlying the training effects in PD, which have not been studied in the previous investigation focusing on healthy elderly with falls (17). We finally plan to use the most recent AR-TT and adapt the AR programs for PD patients with balance deficits by including cueing and perceptual DT.

In summary, the interventions were designed to increase gait automaticity and to compensate for any reduced executive functioning in the course of the disease. Whethermotor-perceptual DT has stronger effects than motor-executive DT or whether the contrary will be the case, cannot be answered so far. The present study may well provide an answer.

